### Cluster randomisation

Within each ambulance service region, stations/teams were eligible for randomisation if the ambulance practitioners attend incidents in geographical areas where suspected stroke patients are usually conveyed to a PSC which makes thrombectomy referrals to the participating CSC. In addition, stations/teams which usually convey directly to the participating CSC were also randomised so that all stations/teams across a region were included. This choice of all stations/teams (ambulance practitioners) across a region was because (1) ambulance practitioners and vehicles are often moved around according to operational service demand and can serve both PSCs and CSCs irrespective of station base/team, hence this approach ensures that all pathway eligible patients will be attended by a randomised ambulance practitioner and (2) the full study population can be identified (see also Study population, below).

Stations within an ambulance service region were only excluded from randomisation if they had a non-routine function and staff would not be deployed to suspected stroke incidents (eg, the station is the base for Hazardous Area Response Team practitioners only), or, if they were in geographical regions where it would be very unlikely that attended patients would be conveyed to a study relevant PSC or CSC. For example, some ambulance service regions serve more than one CSC and staff from specific stations were highly likely to only attend incidents where conveyance was to a PSC which refers to the non-study CSC.

Within each participating region, included stations/teams were allocated 1:1 between intervention and standard care using covariate constrained randomisation,^23^ balanced according to size (defined as total number of staff) and distance from the CSC. Balancing on these variables was to ensure that intervention and standard pathway ambulance practitioners were approximately equally matched in terms of important operational characteristics. For participating regions with more than one included CSC, randomisation was stratified by centre, or centre was used as a covariate in the balance metric, depending on the number of ambulance stations involved.

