### Study intervention

The specialist prehospital redirection pathway (SPEEDY pathway) consists of:

*Initiation* by any grade of ambulance practitioner using information routinely collected during suspected stroke assessment.

Intervention ambulance practitioners initiate the pathway if:

the incident is within a location where routine conveyance is to a PSC which refers to a participating CSC (ie, secondary transfer area).the incident is within the time window agreed by the relevant participating CSC for operating the SPEEDY pathway (eg, 8:00 to 20:00).the standard ambulance practitioner assessment indicates the following clinical criteria:a clinical impression of suspected acute stroke with two symptoms of the standard FAST test both present: arm weakness and speech disturbance.the symptoms began within the last 5 hours, or it is within 5 hours since waking with these symptoms.a low risk of an endangered airway that would require additional urgent medical attention (Alert, Vocal response or Pain response (but not Unresponsive) on the AVPU scale).

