### Outcomes

#### Primary outcome

This study has a co-primary outcome of:

thrombectomy rate.the time from stroke symptom onset to thrombectomy (when thrombectomy is received).

The primary analysis will be conducted using the primary analysis population (see also Study population’, above).

If the stroke symptom onset time is unclear, the ‘last known well’ time will act as the onset time in keeping with standard clinical practice.

Time of thrombectomy will be defined by the time of arterial puncture whether or not thrombus is subsequently removed.

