As a research project, it is not possible to take advantage of systems used to enforce clinically adopted pathways across a large dispersed ambulance workforce such as mandatory audit, staff training and regular feedback. Instead, research relies on softer approaches for engagement such as regular communication and attempting to maintain a positive research culture. Ambulance assessed patients meeting the pathway criteria do not occur frequently for individual practitioners. It is estimated that an average of 1–2 suspected stroke patients per month are assessed by an individual practitioner, but only every 4–6 months will one of these patients fulfil the pathway initiation criteria. Therefore, individual practitioners are required to recognise an infrequent event under time pressure in the uncontrolled prehospital environment, and then remember to deploy a research intervention.

Using this described estimands intercurrent events strategy to define the intervention primary analysis group allows the impact of the pathway to be assessed without influence of an unpredictable deployment rate. This approach also makes the results more generalisable to any healthcare setting (inside and outside the UK) where any future deployment (implementation) rate may differ for different reasons.

*Control primary analysis group*: this comprises only patients where the SPEEDY pathway was NOT initiated. Any patients where the SPEEDY pathway was used will be excluded. This scenario, however, where the pathway is initiated by control assigned staff (in error), should be infrequent due to the cluster design.

*Analysis*: using the estimands defined groups, the co-primary outcomes of thrombectomy rate and time to thrombectomy will be examined using a two-part regression model. The model will be adjusted for predefined baseline covariates and the stratification variables of size of ambulance station and distance from a CSC.

Part 1 of the model will determine the chance of thrombectomy treatment occurring as a binary variable. Part 2 of the model will then analyse time to treatment as a continuous variable, conditional on thrombectomy having occurred.

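### The primary model's named stratification variables do not match the randomisation: region and CSC, which restricted the allocation, are not named in the adjustment set

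*Protocol article*

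**What the plan says.** The Primary analysis section of the protocol article describes a two-part regression: part 1 for whether thrombectomy occurred, part 2 for time to thrombectomy among those treated. It then fixes the adjustment: "The model will be adjusted for predefined baseline covariates and the stratification variables of size of ambulance station and distance from a CSC". The baseline covariates are not listed, and the Statistical analyses section refers all detail to a statistical analysis plan (SAP). The Secondary analyses section repeats the reference to the stratification variables for its adjusted models.

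The Cluster randomisation section describes the allocation differently: "Within each participating region, included stations/teams were allocated 1:1 between intervention and standard care using covariate constrained randomisation", with the allocation "balanced according to size (defined as total number of staff) and distance from the CSC". Where several centres took part in one region, the article adds this rule: "randomisation was stratified by centre, or centre was used as a covariate in the balance metric, depending on the number of ambulance stations involved". The Study timeline section counts five ambulance services and eight CSCs.

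The Primary analysis section and its Table 2 restrict the intervention group to patients for whom the pathway was initiated and contact with the CSC was made. Controls are kept unless the pathway was used for them.

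**The concern.** The article gives a list of stratification variables, and that list does not agree with its own account of the randomisation. Region restricted every allocation. Centre restricted the allocation in multi-CSC regions. An SAP that followed the sentence literally would carry the mismatch into the primary model and into the adjusted secondary models.

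Two things are at stake.

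- **Precision.** Allocation within region balances area differences between arms by design. A model that ignores this still counts those differences as noise, so its standard errors tend to be too large. Time to thrombectomy is tested first and the rate is tested only if time succeeds, so precision on time matters for both outcomes.
- **Bias.** Randomisation balances area mix across all patients of the two arms. It does not do so after one arm has been cut down to patients with pathway contact. The article itself calls deployment unpredictable. If deployment differs by region, the two compared groups can have different area mixes, and any area difference in time or rate then leaks into the estimate. A station random effect does not cure this, because the treatment contrast is made between stations.

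**Working it through.** **Inputs.** From the Sample size section: difference 30 min, SD 120 min, one-sided 5%, power 90%, 150 clusters, intracluster correlation (ICC) 0.01, N = 564. From the Study timeline section: five services, eight CSCs. The share of variance due to region/CSC is not given, so it is treated as an assumption.

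**1. The plan's own figure.** Without clustering, N0 = 4 × [120 × (1.645 + 1.282) / 30]² = 548.1. With the design effect 1 + (N/150 − 1) × 0.01, solving for N gives

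N = 548.1 × 0.99 / (1 − 548.1 × 0.01/150) = 563.2, which rounds up to the stated 564.

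The figure reproduces, and it uses an unadjusted SD.

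**2. Power at N = 564.** Per-observation variance = 120² × (0.99 + 0.01 × 564/150) = 14,400 × 1.0276 = 14,797. SE = √(4 × 14,797 / 564) = 10.24 min. Power = Φ(30/10.24 − 1.645) = 90.0%.

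**3. Gain if the ICC of 0.01 already holds all area variation.** In the extreme case, region/CSC terms remove the whole station-level component. Variance = 14,400 × 0.99 = 14,256, SE = √(4 × 14,256 / 564) = 10.05 min, power = 91.0%. The required N falls to 548.1 × 0.99 = 542.6, about 4% below 563.2.

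**4. Gain if region/CSC explains a further share R² of the variance (assumption).** Residual SD = 120 × √(1 − R²), with the ICC held at 0.01 of the residual variance.

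| R² | Residual SD (min) | N needed (unrounded) | Power at 564 |
|---|---|---|---|
| 0 | 120.0 | 563.2 | 90.0% |
| 5% | 117.0 | 534.0 | 91.3% |
| 10% | 113.8 | 505.0 | 92.5% |

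For scale, a between-CSC SD of 20, 30 or 40 min is 20²/120² = 2.8%, 30²/120² = 6.3% or 40²/120² = 11.1% of the variance.

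**5. How area mix could bias the estimate (illustration; every input is assumed).** Take two equal-sized groups of regions with the same share of patients treated, and deployment of 20% and 60%. The intervention analysis group is then split 0.2/(0.2 + 0.6) = 25% to 75%, while controls stay at 50% to 50%. If mean time differs by 40 min between the two groups of regions, the spurious difference is (0.75 − 0.50) × 40 = 10 min, one third of the 30 min target. A 20 min area difference gives 5 min, and equal deployment gives none. The sign depends on which regions deploy more. The same formula, shift in mix times area difference, applies to the thrombectomy rate in part 1.

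**The case against.** The strongest reply is that the adjustment set is not closed. The unlisted baseline covariates may include region or CSC, and an SAP that is not shown will list them. That stands. A reader might infer that the analysis omits the strata; the document supports only that it does not name them while presenting two balancing covariates as the stratification variables.

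It can also be said that distance from a CSC is already in the model, that the sample size assumes a station random effect, and that standard errors that are too wide are conservative. These points limit the precision argument. They do not answer the area-mix argument, because neither distance nor a station effect represents region or centre. It is also fair that no passage links region to outcome with a figure, and that the pathway's operating window applies to both arms through the population definition.

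A reader might infer that the trial is underpowered. It is not on this ground: 564 reproduces at 90% with an unadjusted SD, so adjustment can only add to the planned power on those inputs.

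A reader might also go further. When onset is unclear, the last-known-well "time will act as the onset time in keeping with standard clinical practice", and eligibility extends to patients who woke with symptoms. One could argue from this that the onset-to-call interval must be a covariate, that the 120 min SD is too small, or that call-to-puncture time should be reported. The document does not support these as findings. The covariate list is ordinary SAP content. The wake-up share and the sleep time are not given. The SD comes from national audit data that may already include such patients. A further supporting outcome is a matter of preference.

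**Conclusion.** The mismatch is real and rests on two sections of the same article. Its demonstrated effect on precision is small: about 1 power point if the ICC of 0.01 covers area variation, and about 1.3 to 2.5 points if region/CSC explains a further 5 to 10% of the variance, which is an assumption.

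The better reason to name region/CSC is protection against area-mix bias in the primary comparison. The size of that bias cannot be derived from the document; the 10 min illustration shows only that modest regional contrasts could matter against a 30 min target. Region/CSC terms would deal with the area component alone. Selection within an area, by which patients had the pathway initiated, would remain. The bias argument does not carry over to the intention-to-treat analysis, where the randomised area mix is kept; there only precision is affected.

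**What to change.** In the Primary analysis section and the SAP, state that both parts of the two-part model adjust for region/CSC as fixed effects, together with station size, distance from the CSC and the listed baseline covariates, and keep the station random effect that the sample size assumes. Describe size and distance as balancing covariates, and region (with centre where it was used) as the restriction on the randomisation. Make the same change wherever the Secondary analyses section refers to the stratification variables.

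Define CSC as the centre attached to the station at randomisation, not the one that admitted or treated the patient, since the destination can be affected by allocation.

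The cost is a wording change made before the unblinded analysis, no new data, and about 8 − 1 = 7 degrees of freedom. CSC terms already contain region if each centre belongs to one region.

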#### Secondary analyses

Using the primary analysis population, a standard ITT approach will be applied to examine the rate and speed of thrombectomy treatment.

Secondary outcomes will be evaluated using both the primary and other analysis populations. According to the type of data, linear or generalised linear models will be used. Both unadjusted analyses and analyses which adjust for predefined baseline covariates and the stratification variables will be undertaken. Analyses will be on a complete case basis, although if required, additional sensitivity analyses will be undertaken using an appropriate imputation method.

#### Performance analyses

The performance of the study intervention pathway for identification of patients suitable for thrombectomy will be determined by calculation of sensitivity, specificity, positive predictive value and negative predictive value.

### Economic evaluation

The economic evaluation will include within-trial cost-effectiveness analyses, cost–utility analyses and calculation of willingness to pay at a range of accepted threshold values. Due to the different study populations contained within the trial, several separate evaluations may be conducted which will be fully detailed in a Health Economic Analysis Plan. The perspective will be that of the English National Health Service and all assumptions will be stated and justified by relevant source data.

For an initial set of cost-effectiveness analyses, incremental effects will be measured in terms of the volume of patients treated and difference in minutes until the start of the thrombectomy procedure for treated patients. Recorded resource usage will enable incremental costs to be calculated using standard reference values for ambulance practitioner and remote specialist time, ambulance journeys, thrombectomy procedures, thrombolysis and hospital bed usage according to diagnostic category. The cost per thrombectomy and per minute of reduction in time until treatment will be reported. A sensitivity analysis will examine the effect of including resource utilisation due to patients who did not receive thrombectomy but underwent a remote assessment and/or were transferred to a CSC.

Further cost-effectiveness analyses will be conducted where effectiveness will be measured in terms of modified Rankin Score at the end of the care episode, ie, final discharge into the community (±local repatriation) or death, to report incremental cost per patient dependency level including death. As it is possible that the specialist prehospital redirection intervention could lead to a relative increase in treatments late within the clinical time window that reduce the overall mean benefit for health, further analysis will specifically examine the cost per independent patient stratified according to the time interval between stroke onset and thrombectomy treatment.

Cost–utility analyses will estimate lifetime incremental cost per quality-adjusted life-year (QALY), following the National Institute for Health and Care Reference Case.^38^ Data from the trial indicative of health status (specifically arterial reperfusion according to TICI score,^39^ clinical recovery according to NIHSS score at 24hours and mRS at discharge)^40 41^ will be combined with reference data about longer term stroke outcomes (quality of life and healthcare utilisation) and lifetables to estimate the lifetime marginal cost utility of the pathway. Data will be incorporated into a Markov model to determine the relative clinical and resource efficiency of the intervention, measured in terms of projected incremental cost per QALY. A cost-effectiveness acceptability curve will be generated using bootstrapped estimates of incremental costs and QALYs to illustrate uncertainty surrounding the cost-effectiveness estimate. The probability that the intervention would be considered cost-effective according to a range of willingness to pay values will also be calculated.

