Selective redirection models have begun to be evaluated and to date there are two published randomised controlled trials (RCTs). In the RACECAT trial^16 17^ (Catalonia, Spain), which reported in 2022, paramedics used the Rapid Arterial oCclusion Evaluation (RACE) scale^18^ as the means of LVO stroke identification and patients scoring greater than 4 (out of 9) points were randomised to redirection to a thrombectomy provider or local admission to the nearest stroke unit. Patients in the intervention group were more likely to receive thrombectomy (OR 1.46 (95% CI 1.13 to 1.89)) and there was a 56 minute reduction in time to treatment. However, thrombolysis treatment was less likely (OR 0.59 (95% CI 0.45 to 0.70)) and slower (34.5 minutes). Overall, there was no effect on patient functional status at day 90 after stroke (aOR 1.03 (95% CI 0.82 to 1.29)). Of the 679 patients included in the redirection (intervention) group, 37% (n=253) received a thrombectomy, therefore 63% of patients were redirected and did not receive thrombectomy treatment. In a secondary analysis published in 2023, concern was raised about poorer outcomes for redirected haemorrhagic stroke patients (141/679 (20.8%)).^19^

The second redirection trial^20^ (conducted in Denmark) which reported in 2023, only recruited 171 of 600 planned patients due to a slow enrolment rate. This study involved a two-step patient assessment which considered both LVO identification and thrombectomy suitability prior to randomisation. Ambulance practitioners firstly used the Prehospital Acute Stroke Severity (PASS) scale, and if patients scored above a threshold (2 or more), this triggered a telephone call to a regional thrombectomy centre. The call taker then determined whether the patient could be a possible thrombectomy candidate, and if so, the patient was randomised to redirection to the CSC or usual care admission to the nearest PSC. Compared with standard care, more of the intervention group received thrombectomy (63% vs 53%), with a reduction in onset to treatment time of 35 minutes (p=0.007). More intervention patients also received thrombolysis (78% vs 67%), but with a delay of 30 minutes (p=0012). Overall, no difference was found in patient functional outcome at day 90 (aOR 1.42 (95% CI 0.72 to 2.82)). Of the 87 patients included in the redirection (intervention) group, 33% (n=29) received a thrombectomy and therefore 67% were redirected without treatment.

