A two-stage process of ambulance practitioner clinical scale assessment triggering a CSC remote review has also been described during a non-randomised observational study of redirection for thrombectomy in Stockholm (published 2020).^21^ Ambulance nurses who suspected stroke based on assessment using the Face Arm Speech Test (FAST) further graded arm and leg strength, and if moderate or severe weakness was present, a thrombectomy centre stroke specialist was consulted by telephone. The call taker assessed likely suitability for thrombectomy and made a decision about whether to convey directly to the thrombectomy centre or to the nearest local stroke centre. Compared with historical controls from the year before, the proportion of patients undergoing thrombectomy after direct admission increased from 24% to 73% (p<0.001), while median onset to thrombectomy time reduced from 206 (IQR 160–280) to 137 minutes (IQR 118–180) (p<0.001). Thrombolysis timings compared with historical controls were unchanged. For 25% of patients, thrombectomy was still accessed through secondary transfer from a PSC, either because they were not initially thought to be suitable during remote prehospital assessment, or because the assessment was not activated due to failure to identify that the patient’s symptoms were possibly due to stroke. Overall, of the patients directly admitted to the CSC, 26% received a thrombectomy and performance characteristics of the assessment process were accuracy of 87% for LVO stroke identification and specificity of 91% for receipt of thrombectomy.

During the time that the above-described studies were ongoing, funding was secured to develop and evaluate a selective redirection model for the UK. Qualitative work during 2021–2022^22^ established the acceptability of a new prehospital pathway which considered the need for accurate identification of patients with LVO stroke and suitability for thrombectomy, as well as the ability for implementation into existing healthcare infrastructure. The pathway comprises the following steps:

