### Sample size

The study is powered using the primary analysis population (as defined above in ‘Study population’). The primary analysis population was chosen because it is the group where direct effects of the intervention can be most appropriately assessed, ie, the population eligible for both pathway deployment and subsequent thrombectomy treatment.

Considering the primary analysis population, the study is powered to detect a clinically meaningful reduction of 30 minutes in the time from stroke onset to thrombectomy and to demonstrate whether there is a change to the thrombectomy treatment rate.

Time to treatment: For 90% power (one-sided 5% significance level) to conclude that the intervention reduces the time from onset to treatment, data from *564* participants are required. This calculation assumes a random effect for clusters (ambulance stations), 1:1 allocation of 150 clusters to the two groups, and an intracluster correlation of 0.01 (based on previous similar ambulance trials which demonstrated minimal clustering).^34 35^ The standard deviation of the onset to treatment time is taken as 120 minutes, based upon available national audit data.^11^

Treatment rate: Assuming a conservative baseline thrombectomy rate of 3% in the total stroke population across centres, an important absolute change in procedures would be 2% (ie, a decrease to 1% or increase to 5%), which is equivalent to a change of 8.4% amongst the primary analysis population (baseline 13.2%, decrease to 4.8% or increase to 21.6%). To confirm whether the intervention changes treatment rates compared with standard care, *894* participants are required to detect an 8.4% difference (using change from 13.2% to 21.6% which gives the higher sample size, two-sided 5% significance level; power 90%; ICC 0.01 for 150 clusters with 1:1 randomisation).

The total size of the primary analysis population, however, will be dependent on CSC thrombectomy rates as this will determine the availability of patients for the time to treatment analysis. Based on previously published work,^11 21^ the investigator team have estimated that the primary analysis population size will be between 2600 and 4300 patients if thrombectomy services are running at 5% and 3% of all stroke patients, respectively.

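### The base-case cost per thrombectomy and per minute saved omits patients who were remotely assessed or transferred but not treated, so it leaves out part of the pathway's incremental cost

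*Protocol article*

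**What the plan says.** The Economic evaluation section of the protocol article begins with a set of analyses in which "incremental effects will be measured in terms of the volume of patients treated and difference in minutes until the start of the thrombectomy procedure", the minutes being measured in treated patients. Resource use is to be valued for "ambulance practitioner and remote specialist time, ambulance journeys, thrombectomy procedures, thrombolysis and hospital bed usage according to diagnostic category". The outputs are then named: "The cost per thrombectomy and per minute of reduction in time until treatment will be reported". The next sentence sets the costing boundary: "A sensitivity analysis will examine the effect of including resource utilisation due to patients who did not receive thrombectomy but underwent a remote assessment". That sentence goes on to cover untreated patients who were transferred to a CSC, whether or not they had a remote assessment.

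The same section then plans cost by modified Rankin level including death, and a lifetime cost per QALY. It refers full detail to a separate health economic analysis plan, which is not shown.

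**The concern.** The pathway finds suitable patients by assessing a larger number. Calls that end in local conveyance, and redirections that end without a procedure, are therefore part of what the health service buys when it adopts the pathway. A base case that counts only treated patients gives the same ratio to a pathway that redirects few unsuitable patients and to one that redirects many, provided the treated patients are the same.

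That matters here. The Background rejects sending every suspected stroke to a CSC because of limited capacity and displacement of ineligible patients, and it says the pathway aims to keep redirection of patients without large vessel occlusion low. The base-case ratio cannot show whether that aim is met. It is also incomplete for the stated English NHS perspective. At stake is a headline cost per thrombectomy or per minute that looks better than the cost of running the pathway.

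**Working it through.** **1. What is in and out of the base case.** The sensitivity analysis looks at the effect of including untreated patients who were assessed or transferred. They are therefore outside the analysis it is compared with. The list of cost items says which resources are valued, not whose.

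**2. Direction.** For arms of equal size, split the incremental cost into a treated part and an untreated part, ΔC = ΔC_T + ΔC_U. The base case keeps ΔC_T and drops

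ΔC_U = a·A + d·R + s·(S_I − S_C)

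- A: remote assessments in untreated patients, at unit cost a.
- R: redirections in untreated patients, at net cost d after allowing for the local admission replaced.
- S_I and S_C: untreated secondary transfers in the intervention and control arms, at unit cost s.

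The first term arises almost only in the intervention arm and is positive. The second is likely to be positive. The third may be negative if the pathway avoids some untreated transfers. So ΔC_U is probably positive, but neither its sign nor its size is guaranteed. The article gives none of a, d or s.

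**3. The plan's own figure.** Sample size gives thrombectomy rates in the primary analysis population as "baseline 13.2%, decrease to 4.8% or increase to 21.6" per cent and a population of 2600 to 4300 for 564 treated patients.

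- 564 / 0.216 = 2611 and 564 / 0.132 = 4273, so the stated range is reproduced.
- The untreated share is 1 − 0.216 = 78.4% to 1 − 0.132 = 86.8%.

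These shares describe the whole primary analysis population under planning rates, not the patients assessed or redirected. They show only that thrombectomy is the minority outcome.

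**4. Untreated share among redirected patients in the cited studies (Background).**

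| Study | Treated | Untreated | Untreated per treated |
|---|---|---|---|
| Catalan trial | 253/679 = 37.3% | 426/679 = 62.7% | 426/253 = 1.7 |
| Stockholm study | 26% | 74% | 0.74/0.26 = 2.8 |
| Danish trial, as 29 of 87 | 33.3% | 66.7% | 58/29 = 2.0 |
| Danish trial, as 63% treated | 63% | 37% | 0.37/0.63 = 0.59 |

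The Catalan figure is stated as "63% of patients were redirected and did not receive thrombectomy treatment" and the Stockholm figure as "of the patients directly admitted to the CSC, 26% received a thrombectomy". The 73% also reported for Stockholm is the share of thrombectomies reached by direct admission, so it does not conflict. The Danish account gives 63% against 53% treated by group, then 29 of 87 treated in the intervention group, hence "67% were redirected without treatment". The 63% and 33% are not consistent as written, and no second denominator is given, so I do not rely on either.

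**5. From patient counts to cost (assumption).** Let u be the untreated share and r the redirection cost of an untreated patient relative to a treated one. The share of redirection cost carried by untreated patients is u·r / (u·r + 1 − u).

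| r | Catalan (u = 0.627) | Stockholm (u = 0.74) |
|---|---|---|
| 1 | 63% | 74% |
| 0.5 | 46% | 59% |
| 0.25 | 30% | 42% |

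Untreated patients carry more than half once r exceeds (1 − u)/u, which is 0.59 (Catalan) or 0.35 (Stockholm). If the thrombectomy procedure is also counted, at k times the redirection cost with r = 1, their share falls below half once k exceeds u/(1 − u) − 1, which is 0.68 or 1.85. The omitted share is thus likely to be material, but the documents do not fix it.

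**The case against.** The strongest reply has four parts.

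- **This is only an initial set of analyses.** The analyses by Rankin level and per QALY follow, and nothing limits them to treated patients. This stands. A reader might infer that the whole evaluation is biased or cannot meet the cost-effectiveness objective, but the text does not support that.
- **The omitted costs are not confined to the intervention arm.** Standard care also transfers patients, and those not then treated fall in the same excluded group. Redirection also replaces a local admission, so its net cost is below its gross cost. This stands too. It makes the direction probable rather than certain, and it means transfers in both arms must be counted.
- **The cited studies may not carry over.** As described, the Catalan trial selected by a paramedic scale alone, whereas this pathway adds a specialist check. The percentages are for scale only.
- **The costing population is left to an unseen plan.** Beds are to be costed by diagnostic category, and in Table 1 those categories include haemorrhage and mimic, which sits awkwardly with treated-only costing. This part does not rescue the text. The split between base case and sensitivity analysis is stated in the article itself.

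The fuller costing is prespecified and will be reported, so nothing is hidden. The question is which version leads.

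**Conclusion.** The point holds for cost per thrombectomy and cost per minute saved. As worded, their base case leaves out part of the pathway's incremental cost and probably favours the pathway. This rests on reading the sensitivity-analysis sentence literally, and on untreated calls and redirections outweighing any saving in untreated secondary transfers.

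The size is unknown. The usable indications are 63% and 74% untreated among redirected or directly admitted patients in two cited studies.

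A reader might go further and conclude that most of the pathway's cost is excluded, or that the ratio is understated by the inverse of the treated share (1/0.37 = 2.7 to 1/0.26 = 3.8). Neither follows. Those factors scale gross redirection cost with equal cost per patient. The reported ratio is an incremental cost that also includes procedures, thrombolysis and beds, and no unit costs are given.

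**What to change.** - **Cost per thrombectomy.** Make the base case (C_I − C_C) / (p_I − p_C). C is the mean cost per patient and p the thrombectomies per patient, both over all patients in each arm of the target population, including mimics, haemorrhages and untreated patients. Count transfers in both arms.
- **Cost per minute.** Minutes exist only for treated patients, so numerator and denominator cannot share the whole population. Report the ratio with its costing population stated.
- **Treated-only costing.** Keep it as the sensitivity analysis.
- **Mimics.** They have no national audit record, so state the assumption used for their bed costs.
- **Later analyses.** State the costing population for the Rankin and QALY analyses as well.

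The cost is wording in the protocol and the health economic analysis plan, plus a little more analysis. The call log records each pathway call, and the ambulance exports cover suspected strokes including mimics, so no new collection is needed for calls and journeys. The downside is a ratio that is likely to be less favourable. The change should be made before the analysis, since first results are expected in summer 2026.
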